**Results:**

A total of 160 participants were recruited and randomized between January 4 and 12, 2024. Baseline assessments were conducted from January 28 to February 1, 2024. The psychotherapy training program for the intervention group took place on February 3 and 4, 2024. Posttraining assessments were conducted starting April 1, 2024. Due to withdrawals, incomplete surveys, and data loss, we had a total of 113 participants: 57 in the intervention group and 56 in the control group. The amount of data varied across measures. The data analysis was finished in August 2024.

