### Sample Size and Power Calculation

The sample size was calculated based on the primary outcome using G*Power [14] (version 3; Universität Düsseldorf). As the data were continuous variables and analysis of covariance (ANCOVA) would be used to compare differences between the 2 groups, an a priori analysis selecting ANCOVA as the statistical test was conducted to determine the required sample size. As only a few studies have examined the effectiveness of psychotherapy training for medical students, we were unable to reference effect size or other data as criteria. Therefore, a medium effect size for the primary outcome was estimated preliminarily. It was determined that 128 participants (64 in each group) would be required to achieve 80% power (effect size *f*=0.25; 1 – β=0.80; α=.05). To account for potential attrition, we aimed to recruit approximately 160 participants (80 in each group), ensuring that the proposed analysis would be sufficiently powered even if 25% of participants in each group were lost to attrition.

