### Randomization and Group Allocation

This study aimed to recruit approximately 160 participants, with about 80 in each group. The study coordinator randomized participants into the intervention and control groups using a random number generator in R software, maintaining a 1:1 ratio for allocation to the experimental and control conditions. Participants in the intervention group first received the experimental condition, which included the psychotherapy training program after the baseline assessment. The waitlist control group received the control condition, meaning they participated in the psychotherapy training program only at the end of the study. The timeline of the study was as follows: all participants underwent a baseline assessment, the intervention group received the training program, and the control group received a control training program. After 8 weeks, all participants were followed up, and finally, the control group received the intervention training program (Figure 1).

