### Data Analysis

All data were automatically collected via WenJuanXing through a WeChat-based link. The data were downloaded from the WenJuanXing database into a user-specific Excel file. This study did not include interim analyses; data were analyzed only after all had been collected. The trial statistician blinded the intervention assignment in the data using R software (R Foundation for Statistical Computing) and SPSS (2013 release; IBM Corp.).

The primary hypothesis was that, compared with the control intervention, the intervention group receiving the psychotherapy teaching program would significantly gain more knowledge about psychotherapy after training. We also hypothesized that the program would lead to increased utilization of psychotherapy and be associated with improvements in knowledge. The third hypothesis posited that trainees’ self-reported self-efficacy and motivation to apply psychotherapy in clinical practice would increase significantly.

Descriptive statistics were used to assess demographic and psychotherapy-related characteristics at baseline. Following normality and homogeneity of variance tests, ANCOVA was used to analyze the primary outcomes. In the ANCOVA model, the dependent variable was the change in the knowledge score. The fixed factor was the group (intervention group or control group), while the covariates included the mean score of psychotherapy knowledge at baseline and years of psychotherapy experience. Pearson correlations and regression analysis (both linear and binary regression models) were used to explore factors associated with the knowledge score at baseline and to assess the increase in psychotherapy utilization in both the intervention and control groups. The secondary outcomes—participants’ psychotherapy utilization, confidence, and motivation—will also be analyzed in the same manner as knowledge.

A complete case analysis was performed, excluding any participants with missing information on the posttraining assessment. Additionally, a sensitivity analysis of the missing data was conducted to determine whether the missingness is random. Demographic information and scores for psychotherapy knowledge, utilization, confidence, and motivation at baseline were compared between the complete data group and the missing data group. All tests were 2-tailed, with a significance level set at *P*<.05.

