## Results

This study recruited 160 participants from January 4 to January 12, 2024. The 2-day training program took place on February 3 and February 4, 2024, and the posttraining assessment was completed on April 1, 2024. Due to withdrawals, incomplete surveys, and data loss, we had a total of 113 participants: 57 in the intervention group and 56 in the control group. The amount of data varies for each measure. Data analysis was completed in August 2024. The results will be published in peer-reviewed journals. If found to be effective, the psychotherapy training program and the accompanying program booklet will be made freely available to the public by the end of the trial.

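### The missing-data sensitivity analysis the article describes, a baseline comparison of completers and non-completers, cannot determine whether missingness is random and gives no second estimate of the effect after 29.4% loss

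*Protocol article*

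**What the plan says.** The Data Analysis section makes a complete-case ANCOVA of change in knowledge the primary analysis, with group as factor and baseline knowledge and years of psychotherapy experience as covariates. Participants without post-training data are left out. It then states that "a sensitivity analysis of the missing data was conducted to determine whether the missingness is random". The next sentence gives the content: demographic data and baseline scores for knowledge, utilization, confidence and motivation "were compared between the complete data group and the missing data group". The article describes no other missing-data analysis.

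On the extent of loss, the abstract says "A total of 160 participants were recruited and randomized between January 4 and 12, 2024", and the Results section says "we had a total of 113 participants: 57 in the intervention group and 56 in the control group". It names the causes ("Due to withdrawals, incomplete surveys, and data loss") but does not break the losses down by cause within arm.

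**The concern.** The comparison is given a task it cannot perform. Whether missingness is at random, in the sense that matters for the primary analysis, depends on how non-response relates to the week-8 knowledge score once arm and covariates are accounted for. The week-8 scores of those lost were never seen. A baseline difference between completers and non-completers counts against missing completely at random. The absence of one establishes nothing about random missingness, and neither result separates missing at random from missing not at random.

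Two further limits follow from the description. The comparison names two groups, complete and missing, and no split by arm, so opposite selection in the two arms could cancel. It also yields no alternative estimate of the treatment effect, so it does not test how far the conclusion depends on the missing data.

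At stake is the reading of the primary result. The outcome is self-rated, and only the intervention arm had the training and the supervision meetings, so reasons for not responding could differ between arms.

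**Working it through.** **1. The plan's own figure.** For ANCOVA with f = 0.25, two-sided alpha 0.05 and noncentrality N × f², N = 128 gives power 0.801. This reproduces the statement in Sample Size and Power Calculation that "128 participants (64 in each group) would be required to achieve 80% power".

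**2. Loss.** 160 − 113 = 47, and 47/160 = 29.4%. The article gives "maintaining a 1:1 ratio for allocation to the experimental and control conditions" but no exact randomised count per arm. If it was 80 each, loss is 23/80 = 28.75% (intervention) and 24/80 = 30.0% (control). Both exceed the 25% allowed for. At N = 113 and f = 0.25, power is about 0.75.

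**3. Power of the baseline comparison.** With 47 against 113 participants, the SE of a standardised difference is √(1/47 + 1/113) = 0.174. For a true baseline difference of 0.3 SD, z = 0.3/0.174 = 1.73, and power is Φ(1.73 − 1.96), about 41%. For 0.4 SD it is about 63%. A null result is weak evidence even about baseline.

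**4. What the comparison can detect, by dropout mechanism.** Assumptions, none from the article: 80 per arm, true effect 0.50 SD, about 29% outcome-related loss in the intervention arm (low scores or gains more likely to be lost), 30% random loss in control, baseline-outcome correlation 0.3 to 0.6, log-odds slopes 0.5 to 2, baseline test pooled over arms.
- The complete-case ANCOVA estimate is about 0.58 to 0.84 SD across these settings.
- If dropout depends on the part of the outcome that is independent of baseline, the baseline test rejects in about 5% of runs. That is its nominal rate and follows from the mechanism chosen.
- If dropout depends on gain or on the week-8 score itself, it rejects in about 7% to 59% of runs.
- If the same selection acts in both arms, the estimate is about 0.49 to 0.51 SD, so bias is near zero.

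**5. With no true effect.** For the baseline-independent mechanism in the intervention arm only, correlation 0.5 and 4,000 trials per setting, slopes of 0.5, 1.0 and 1.5 give:
- bias of 0.12, 0.21 and 0.27 SD;
- type I error of 12%, 25% and 41%;
- baseline-test rejection of 5.3%, 5.2% and 4.9%.

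**6. What an analysis of the effect would show.** Suppose the observed effect is 0.5 SD (assumed) and the 23 missing intervention participants did worse by delta SD than the observed data predict, with missing controls as predicted. The effect becomes 0.5 − delta × 23/80:
- delta 0.25: 0.43;
- delta 0.5: 0.36;
- delta 0.75: 0.28;
- delta 1.0: 0.21.

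If missing intervention participants gain only what controls gain, the effect is 0.5 × 57/80 = 0.36. Holding the SE at √(1/57 + 1/56) = 0.188, significance is lost at delta = (0.5 − 1.98 × 0.188)/0.2875, about 0.44 SD. Baseline adjustment shrinks the SE. At correlation 0.5 it is 0.188 × √0.75 = 0.163, and the point moves to (0.5 − 1.98 × 0.163)/0.2875, about 0.62 SD.

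**The case against.** The strongest case on the other side has four parts.

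- **The ANCOVA already adjusts for baseline.** This stands. If missingness depends only on arm, baseline knowledge and years of experience, and the model is right, the complete-case estimate is valid. Only residual outcome-related dropout is left.
- **The baseline check is not blind.** This also stands. Baseline knowledge is a proxy for week-8 knowledge, so the check has some power against dropout driven by gain or by the week-8 score. A reader might infer that it carries no information; the 7% to 59% range shows otherwise. It is an unreliable signal, and it still cannot establish randomness.
- **Nothing shows that the result is biased.** Correct. A reader might infer from 29.4% loss that the effect is inflated. The article does not support that: retention was nearly equal (57 and 56), incomplete surveys and data loss need not track the outcome, and selection common to both arms leaves almost no bias. Equal rates do not prove equal mechanisms, so the risk is untested rather than demonstrated.
- **More may exist outside the article.** An analysis plan, not shown, could hold further sensitivity analyses. The point therefore concerns only the one analysis described here and the purpose given to it. That purpose is wrong as written, whatever another document adds.

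It is also tempting to read the comparison as the ground for choosing complete cases. The article attaches no such decision rule. Nor does it say whether the comparison was additionally made within arms.

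The Withdrawal From the Program section says non-responders were kept in the analysis by randomised group, but gives no method and then also states a complete-case analysis. That is a separate inconsistency and does not supply the missing analysis.

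**Conclusion.** The point holds in a limited form. The stated sensitivity analysis cannot do its stated job: it can contradict missing completely at random, but it cannot determine that missingness is random, and it tests no conclusion about the effect. With 47 of 160 lost, this leaves residual outcome-related dropout that differs between arms unexamined in the article.

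The size depends on assumptions that the article cannot settle. With selection in the intervention arm only, the complete-case estimate is too high by about 0.08 to 0.34 SD (0.58 − 0.50 and 0.84 − 0.50). With equal selection in both arms, bias is near zero. Because the amount of data varies by measure, missingness for knowledge may also differ somewhat from 29.4%. The article does not show that the complete-case result is biased. It should be corrected before the results are interpreted.

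**What to change.** 1. Describe the comparison of complete and missing groups as descriptive, show it separately by arm, and remove the statement that it determines whether missingness is random.
2. Add an analysis of the primary outcome in all 160 randomised, for example multiple imputation by arm, followed by delta-adjusted or reference-based steps. Include the case in which intervention non-responders gain only what controls gain, and report the shift at which the conclusion is lost. Other analyses that vary the missing-data assumption openly would also serve.
3. Label the addition post hoc, because data analysis was finished in August 2024.

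The cost is a few lines of text and code. No new data are needed: the Primary Outcome section reports baseline knowledge for 160 participants.

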### Safety and Adverse Events

Throughout the psychotherapy training program, adverse events were closely monitored. Participants were encouraged to communicate any psychotherapy-related issues or adverse events encountered during their clinical work. We prompted each participant to report any adverse events experienced at each group meeting, and they could also report them at any time. If participants experienced severe adverse events, they were encouraged to seek support from a psychologist or psychiatrist.

We did not anticipate any training-related serious adverse events (SAEs), such as life-threatening incidents, during this trial. However, if any adverse events occur, we will document the SAE, record it on the SAE form, and submit it to the ethics committee of Sir Run Run Shaw Hospital (the principal investigator’s affiliation) within 24 hours.

### Ethics Approval and Consent to Participate

This study was approved by the ethics committee of Sir Run Run Shaw Hospital, an affiliate of Zhejiang University School of Medicine (2024 Ethics Approval File No. 2024-0066). The trial was conducted in accordance with the Declaration of Helsinki. Participants were provided with informed consent before the baseline assessment. After thoroughly reading and understanding the content of the consent, they received a link to electronically sign their name at the end of the informed consent form and submit it via WeChat. Each participant was informed about the study’s purpose, procedures, measurements, potential risks, and benefits before recruitment. Informed consent was then obtained from each participant. Participation was entirely voluntary, and participants could withdraw from the study at any time. Coordinating researchers’ contact information was provided to all participants for any inquiries or concerns.

### Data Security

The authors utilized the professional version of WenJuanXing, which features high-level security management, alongside an applet on WeChat that ensures the secure and confidential protection of participants’ data.

## Results

This study recruited 160 participants from January 4 to January 12, 2024. The 2-day training program took place on February 3 and February 4, 2024, and the posttraining assessment was completed on April 1, 2024. Due to withdrawals, incomplete surveys, and data loss, we had a total of 113 participants: 57 in the intervention group and 56 in the control group. The amount of data varies for each measure. Data analysis was completed in August 2024. The results will be published in peer-reviewed journals. If found to be effective, the psychotherapy training program and the accompanying program booklet will be made freely available to the public by the end of the trial.

In conclusion, this is the first RCT to evaluate the efficacy of a multimodal psychotherapy training program for medical students in China. If this educational program, which offers brief and short-term psychotherapy skills training, proves effective, its nationwide expansion could have a significant health impact. It provides evidence-based psychotherapy training—primarily in CBT—for medical students, and its dissemination will equip HCPs to better manage mental health issues, such as stress and depression. Therefore, it is crucial to develop effective psychotherapy training that emphasizes basic psychotherapy skills. The results of this training’s effectiveness can offer valuable insights for the future development of training programs, enabling them to better meet the learning needs of medical professionals and enhance doctor-patient relationships.

## Appendix

Multimedia Appendix 1 The details of the 2-day psychotherapy training program.

## Abbreviations

ANCOVA: analysis of covariance
CBT: cognitive behavioral therapy
HCP: health care provider
RCT: randomized controlled trial
SAE: serious adverse event
